**Figure 2 F2:**
[figure not shown]
**Evaluation design accounting for seasonal differences and using a waiting list control**. CONT = gym lessons (existing state-sponsored programme). INT = participatory parent-focused intervention plus simultaneous gym lessons. X1 and X2: randomization time points, X1 = autumn, X2 = spring. ---- children enrolled and measured, but no intervention/gym lessons.

Preschool assignment was blinded through the use of sequentially numbered, sealed envelopes. Preschools in the control arm (CONT) (n = 20; 371 children) receive the state-sponsored programme's gym lessons over six months as the sole intervention. Parents of children enrolled at preschools in the intervention arm (INT) (n = 17; 370 children) receive the participatory intervention, while their children also participate in the gym lessons. The participatory parent-focused intervention runs simultaneously with the gym lessons over the first six months, but continues for a total of at least nine months.

To account for seasonal differences in physical activity [34,35], the study was implemented at two time-points during the year: half of the preschools started the intervention in autumn 2008 with the other half starting in the spring 2009. To account for changes that occur as a consequence of physical maturation in children over time, the participatory intervention arm served as waiting list control during the first six months. Due to the participatory nature of the intervention, it was not possible to blind study participants or intervention providers. However, those involved in outcome assessment will be blinded to intervention assignment.

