### Research Questions

We aim to show that the supplementation of state-sponsored gym lessons with a parent-focused participatory intervention:

1) leads to significantly increased physical activity intensity in preschool-aged children at 6 months compared with baseline, as measured by accelerometry

2) leads to significant decreases at 6 months compared with baseline in childrens' mean BMI, sum of skin folds and waist-to-height ratio

3) leads to significant improvement in childrens' PA behaviour at 6 months as assessed by questionnaire

4) leads to a significant increase from baseline in childrens' mean 1-minute heart rate recovery after submaximal exercise at 6 months

5) has sustained effects on primary and secondary outcomes stated above (i.e., no significant difference between 6 and 12 months measurements)

Research questions to be addressed using *qualitative techniques *include:

1) How well is the participatory intervention accepted and adopted by parents and teachers?

2) To what extent do participants feel the parent-focused participatory intervention is tailored to the local needs?

3) Do participants feel that the participatory intervention is feasible in the German preschool setting within the framework of an existing state-sponsored programme?

4) What are the barriers and facilitating factors that appear to impede or promote successful intervention implementation and outcomes?

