### Assessment of intervention effectiveness

The intervention effectiveness is assessed by an intention-to-treat analysis.

Descriptive statistical analysis will be performed on all outcome measures. If needed, data will be transformed to better meet the assumptions of standard inferential statistical tests. We will use multilevel models to account for the structure of our data and for missing data on any of the measurements. In the multilevel model, repeated measurement of outcomes for each child will be considered the first "level"; these data are nested within preschools, which represent the second level. Differences between intervention and control group in primary and secondary outcomes will be analyzed in terms of fixed effects in the multilevel regression model, with age, sex, SES, immigration status and baseline BMI/accelerometer counts included as covariates on the individual level. In secondary analyses, the effect moderation by the preschool context as rated by qualitative data, as well as the level of implementation and adoption of the intervention will be analyzed.

Previous work documents a higher prevalence of overweight [63] and lower levels of physical activity [64] among immigrants. Because of the potential public health implications, we will conduct subgroup analyses at the child level comparing outcomes for normal-weight versus overweight children and for immigrant versus non-immigrant children. Subgroup analyses at the preschool level will be performed for rural versus non-rural locations and intervention timing (autumn versus spring) to assess the presence of potential effect modifiers.

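### Research question 5 takes a non-significant difference between the 6- and 12-month measurements as proof that the effect is sustained

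*Protocol article*

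**What the plan says.** Under Research Questions, the fifth quantitative question defines maintenance: the intervention "has sustained effects on primary and secondary outcomes stated above (i.e., no significant difference between 6 and 12 months measurements". No margin, confidence interval or contrast with the control arm accompanies it, and the article states no other quantitative criterion for judging maintenance.

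The questions share the lead-in "We aim to show that the supplementation of state-sponsored gym lessons with a parent-focused participatory intervention". Question 1 then reads "leads to significantly increased physical activity intensity in preschool-aged children at 6 months compared with baseline, as measured by accelerometry". Questions 2 and 4 are also phrased as change from baseline; question 3 names no baseline ("leads to significant improvement in childrens' PA behaviour at 6 months as assessed by questionnaire").

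The planned analysis is between arms. Assessment of intervention effectiveness states: "Differences between intervention and control group in primary and secondary outcomes will be analyzed in terms of fixed effects". Sample size and power considerations sizes the trial on a difference between intervention and control.

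Three design facts bear on the 6-to-12-month comparison:

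- Evaluation Design places the 6-month visit at the end of the gym lessons.
- Recruitment and randomization says that the parent intervention continues for at least nine months in total.
- The same section names season and physical maturation as sources of change and says that "half of the preschools started the intervention in autumn 2008 with the other half starting in the spring 2009".

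**The concern.** The wording after the i.e. in question 5 is a decision criterion, and it points the wrong way. A test that fails to reject may do so because nothing changed or because the data are too imprecise to show the change. Dropout, device failure or large between-preschool variation would all help the trial to claim sustained effects. Nor does the rule distinguish direction: if the effect grew significantly between 6 and 12 months, which is possible while the parent intervention is still running, the criterion would not be met.

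The rule also looks at measurements at two times, not at the difference between arms. Between those visits the gym lessons stop, the children age and the season reverses. The between-arm effect could hold fully while the rule fails, or fade while the rule passes.

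Sustainability is a main reason given for the participatory approach (Background, Theoretical Model, Discussion), and question 5 covers the primary outcome as well as the secondary ones. A positive claim would rest on an absence of evidence.

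**Working it through.** **1. What the trial is sized for.** Inputs from Sample size and power considerations: difference 0.5 SD (19.05 of 38.1 counts/15 s), two-sided alpha 0.05, power 0.9, ICC 0.1, 504 children in 24 preschools, hence 504/24 = 21 per preschool.

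- Per arm before clustering: 2 × (1.960 + 1.282)² / 0.5² = 84.06.
- Design effect: 1 + (21 − 1) × 0.1 = 3.
- Total: 2 × 84.06 × 3 = 504.4, against 504 stated; 504 / 0.9 = 560, as stated.

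The plan's figure reproduces, and it is a between-arm calculation. Nothing in that section sizes a maintenance claim.

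**2. How often a real loss would pass as sustained: within-arm test.** The documents give no within-child correlation, no correlation over time of preschool means and no size for the seasonal swing, so these are assumptions. The 17 intervention preschools and the ICC of 0.10 are from the article. Assumed are 20 children per preschool, correlation 0.5 between a child's two visits, correlation 0.8 between a preschool's two means, and a seasonal shift s entering as extra variance between preschools.

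- Preschool part of the change variance: 2 × 0.10 × (1 − 0.8) = 0.04.
- Child part: 2 × 0.90 × (1 − 0.5) / 20 = 0.045.
- SE = √((0.04 + 0.045 + s²) / 17) in SD units.
- P(not significant) = Φ(1.96 − loss/SE) − Φ(−1.96 − loss/SE).

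| s (SD) | SE | Loss 0.125 SD | Loss 0.25 SD |
|---|---|---|---|
| 0 | 0.071 | 58% | 6% |
| 0.3 | 0.101 | 77% | 31% |
| 0.5 | 0.140 | 86% | 57% |

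A loss of 0.25 SD is half the planned effect (0.25 × 38.1 = 9.5 counts/15 s); 0.125 SD is a quarter of it (4.8 counts).

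The seasonal rows are approximate. If the two start waves are near-equal fixed halves, the shifts nearly cancel in the mean. The true sampling error then stays near 0.071, and only the estimated SE of a test that omits wave is inflated. For the 0.25 SD loss this gives Φ((1.96 × 0.101 − 0.25)/0.071) = 23% and Φ((1.96 × 0.140 − 0.25)/0.071) = 64% (unrounded SEs used), in place of 31% and 57%.

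**3. Does a between-arm test of the same form help?** Assume the planned size (252 per arm, 12 preschools per arm), within-child correlation ρ of 0.3 to 0.7 and ICC of the change of 0 to 0.1. Within arm, SE² = 2(1 − ρ) × design effect / 252; between arms, twice that.

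| Loss (SD) | Within arm | Between arms |
|---|---|---|
| 0.125 | 27–84% | 56–90% |
| 0.25 | 0–51% | 5–72% |
| 0.5 (all) | 0–3% | 0–22% |

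The between-arm contrast removes drift common to both arms, but its larger SE makes non-significance easier to obtain. Moving question 5 into the multilevel model without changing the rule would not repair it.

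**4. Season, from the dates.** Starts in autumn 2008 and spring 2009 with visits six months apart put the 6- and 12-month visits of every preschool in opposite seasons.

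**The case against.** The strongest reply is that the research questions are aims and the analysis is fixed elsewhere. For questions 1 to 4 this stands. A reader might infer from the change-from-baseline phrasing that the trial judges effectiveness within the intervention arm and never measures the intervention effect. The documents do not support that. The lead-in makes gym lessons alone the implied comparator. The Abstract, Assessment of intervention effectiveness and the sample size section all fix a between-arm comparison. Question 3 names no baseline, and heart rate recovery (question 4) is restricted to descriptive and exploratory use in its own section. Age is a covariate for BMI, and the control arm removes drift common to both arms. What remains is loose wording in questions 1, 2 and 4.

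Three further points carry weight:

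- Question 5 speaks of effects already stated, so it can be read as applying only after success at 6 months. The article does not say so, but the claim that the rule passes with no effect at all should not be pressed.
- Autumn and spring starts make seasonal shifts run in opposite directions and largely cancel in a pooled mean, and an autumn-versus-spring subgroup analysis is planned. Season is therefore more a source of noise than of bias, and the larger probabilities in the first table require that wave be left out of the model.
- Maintenance is also explored through head-teacher interviews at 12 months, and the powered between-arm comparison is untouched.

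None of this rescues the criterion in question 5: the between-arm analysis supplies the right contrast but no sound rule for calling the effect sustained.

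**Conclusion.** The point holds for question 5. As written, it treats failure to reject as evidence of maintenance, has no margin, would count a significantly larger effect as not sustained, and compares time points instead of the intervention-minus-control effect. This fault does not depend on any assumed figure.

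Its size does. Under the first set of assumptions, a 0.125 SD loss passes about 58% of the time without seasonal swing. A 0.25 SD loss passes about 6% of the time, rising to 31–57% only with assumed unmodelled swings of 0.3 to 0.5 SD. These are illustrations, not figures from the documents, and the second set of assumptions shows how widely they move.

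Questions 1, 2 and 4 need a wording correction only. The main 6-month between-arm comparison is not in doubt on this ground.

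**What to change.** Replace question 5 with two estimates from the multilevel model already planned:

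- (a) the intervention-minus-control difference at 12 months, with 95% confidence interval;
- (b) the change in that difference from 6 to 12 months, with 95% confidence interval.

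Call an effect sustained only if all three conditions hold: an effect was shown at 6 months; the 12-month difference excludes zero in the favourable direction; and the interval for the loss lies within a margin fixed in advance. The margin should be in counts or SD units. A fraction of the estimated 6-month effect would be set by the data. The conditions should be joined by 'and': a 12-month difference that merely excludes zero can follow loss of most of the effect, and a bounded loss alone can be met where there was little effect to lose.

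Reword questions 1, 2 and 4 as between-arm differences at 6 months, consistent with the analysis section.

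Cost: rewording, one additional contrast from the same model, and agreement on a margin. A sustained claim becomes harder to make, and because the trial was not sized for it, the interval in (b) may be too wide to support one.

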### Covariates/confounders

For correct interpretation of changes in the primary outcome, we are gathering information on factors or characteristics that may affect both the adoption of the intervention [52] and its effectiveness in inducing change. Confounding factors at the child's level include age, gender [53], socioeconomic status (SES) [54] and immigrant background [55]. Sociodemographic information is collected mainly through the parent-completed questionnaire. Immigrant status of each child, for example, is determined by responses to three items: 1) child is a non-German national, 2) child's parents are native speakers of a language other than German 3) child primarily speaks a language other than German at home [56]. Responses (yes = 1; no = 0) were added to create a final value. The measurement of the child's SES is determined from his/her parent's self-report of the highest level of educational attainment [57,58].

The perceived health status of the child and his/her membership in a sports club might moderate the intervention effect [59]. Information on these characteristics therefore is gathered by the following two questions "How would you describe your child's health status?" ("very bad - very good") and "Does your child regularly engage in PA in a sports club or a similar organization?" ("no", "yes, twice monthly", "regularly one hour/week", "regularly two hours per week", "regularly more than two hours per week", "don't know").

### Process measures

We carefully examine the extent to which the intervention is adopted and implemented and whether features of the context in which the intervention is delivered mediate or moderate intervention outcomes. Mediating factors were defined as contextual factors predisposing for or enabling the intended behavioural change, which might lie on the causal pathway from intervention to outcome. Moderating factors were qualitative or quantitative variables that might affect the direction or strength of the relation between intervention and outcome [60]. General Systems theory, for example, suggests the degree of teacher or parent commitment, the co-existence of other preschool programmes and the preschool physical environment as moderating factors. We therefore conduct a thorough process evaluation, which consists of face-to-face, semi-structured key informant interviews with the head teacher at each site and each measurement point. Interviews have been recorded and are currently being transcribed. These data serve as the basis for qualitative analyses to identify emerging issues related to intervention implementation.

#### Measuring the preschool context

The preschool context is assessed by interview questions in order to reveal teachers' expectations of the intervention, perceived level of parental commitment, physical space for recreation (e.g., the availability of outdoor and indoor areas for physical activity), preschool policies concerning physical activity, and existence of concurrent programmes. These data are supplemented by a brief, structured questionnaire to be completed by the head teacher at each preschool on a range of topics including the number of PA promoting toys and daily hours spent outdoors by children at the site. For operationalizing the preschool context as variable, we established a rating system based on the extent to which the preschool allowed and fostered children's PA. Specifically, seven predefined preschool characteristics (e.g. daily time outside, outside space, number of PA promoting toys) will be rated to yield an overall degree of PA facilitation with a possible range from 0 to 53 points for each preschool.

#### Indicators of intervention adoption and implementation

According to the RE-AIM framework [61,62], evaluations of health promotion interventions should not only focus on efficacy, but should include other dimensions of quality like intervention adoption, implementation and maintenance. In our study, the intervention adoption is being assessed by structured interviews with the head teachers before the intervention start and was rated over all preschools on a 1-100% scale. The extent to which the intervention was implemented at each site is assessed by the external PA teacher delivering the state-sponsored gym programme. This external teacher documents numerous features of the implementation process, including the number of project ideas chosen and finally realized, the number of meetings with parents, the participation rate at these meetings, the barriers and resources perceived by parents and teachers, the social environment and development of issues related to effective communication (e.g. atmosphere during meetings, involvement of immigrant parents, coordination between parents and teachers). In addition, information on implementation gathered during the head teacher interviews at each preschool will be used in the analysis. Based on both these data sources, we currently develop definitions for each of the implementation components as well as a ranking system for each component, rated from 1 = ("not realized") to 3 ("completely realized"). Ratings will then be summarized to yield an overall degree of implementation. Intervention maintenance will be explored through interviews with preschool head teachers at 12 months, with data focusing around the extent to which the parents' projects have become an enduring part of the preschool's activity repertoire.

### Assessment of intervention effectiveness

The intervention effectiveness is assessed by an intention-to-treat analysis.

Descriptive statistical analysis will be performed on all outcome measures. If needed, data will be transformed to better meet the assumptions of standard inferential statistical tests. We will use multilevel models to account for the structure of our data and for missing data on any of the measurements. In the multilevel model, repeated measurement of outcomes for each child will be considered the first "level"; these data are nested within preschools, which represent the second level. Differences between intervention and control group in primary and secondary outcomes will be analyzed in terms of fixed effects in the multilevel regression model, with age, sex, SES, immigration status and baseline BMI/accelerometer counts included as covariates on the individual level. In secondary analyses, the effect moderation by the preschool context as rated by qualitative data, as well as the level of implementation and adoption of the intervention will be analyzed.

Previous work documents a higher prevalence of overweight [63] and lower levels of physical activity [64] among immigrants. Because of the potential public health implications, we will conduct subgroup analyses at the child level comparing outcomes for normal-weight versus overweight children and for immigrant versus non-immigrant children. Subgroup analyses at the preschool level will be performed for rural versus non-rural locations and intervention timing (autumn versus spring) to assess the presence of potential effect modifiers.

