**Methods/Design:**

Thirty-seven South German preschools were identified for this study and agreed to participate. Using a two-armed, controlled cluster-randomized trial design we test a participatory intervention with parents as the primary target group and potential agents of behavioural change. Specifically, the intervention is designed to engage parents in the development, refinement and selection of project ideas to promote PA and in incorporating these ideas into daily routines within the preschool community, consisting of children, teachers and parents. Our study is embedded within an existing state-sponsored programme providing structured gym lessons to preschool children. Thus, child-based PA outcomes from the study arm with the parent-focused intervention and the state-sponsored programme are compared with those from the study arm with the state-sponsored programme alone. The evaluation entails baseline measurements of study outcomes as well as follow-up measurements at 6 and 12 months. Accelerometry measures PA intensity over a period of six days, with the mean over six days used as the primary outcome measure. Secondary outcomes include childrens' BMI, a sum of averaged skin fold thickness measurements across multiple sites, and PA behaviour. Longitudinal multilevel models are used to assess within-subject change and between-group differences in study outcomes, adjusted for covariates at the preschool and individual levels. Teacher qualitative interviews monitor the intervention implementation process.

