### Evaluation Design

Our study uses a cluster-randomized trial design, with natural preschool-bound clusters of children randomized to either the intervention or control arm. The evaluation strategy combines both quantitative and qualitative data collection and analyses. Quantitative outcome measurements will be obtained before the start of the intervention (baseline assessment), 6 months after baseline assessment (at the end of the state-sponsored gym lesson programme) and at 12 months after baseline assessment. Qualitative data collection, described in greater detail below, will allow for a closer examination of variation in the implementation process across and within intervention sites. In reporting our study, we will account for the recommendations of the CONSORT statement concerning complex cluster-randomized trials [31,32]. Baseline data from the completed recruitment to the study will be reported elsewhere.

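### The outcome model names measurements and preschools as its levels and leaves out the child, which misstates standard errors for the 6-to-12-month change and for child-level subgroup comparisons

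*Protocol article*

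**What the plan says.** The section Assessment of intervention effectiveness numbers the levels of the model. On the first: "repeated measurement of outcomes for each child will be considered the first" level. On the second: "these data are nested within preschools, which represent the second level". No level, random effect or covariance for the child is mentioned.

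The same section gives the purpose of the model: "We will use multilevel models to account for the structure of our data and for missing data on any of the measurements". It lists age, sex, SES, immigration status and "baseline BMI/accelerometer counts included as covariates on the individual level". It also plans child-level subgroup comparisons by weight status and by immigrant background.

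The abstract (Methods/Design) describes the analysis thus: "Longitudinal multilevel models are used to assess within-subject change and between-group differences in study outcomes". The measurement times are stated there too: "The evaluation entails baseline measurements of study outcomes as well as follow-up measurements at 6 and 12 months".

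Under Research Questions, item 5 treats the absence of a statistically significant difference between the 6- and 12-month measurements as evidence that effects are sustained.

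**The concern.** The data have three nested levels: visits within children, and children within preschools. With baseline used as a covariate, each child still has up to two outcome values. If only the preschool carries a random effect, stable differences between children go into the residual. The model then knows nothing of the likeness between a child's own two values beyond what any two children in that preschool share.

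That does not fit the promised analysis of within-subject change. It also weakens the handling of missing measurements, because a child's value at one follow-up adds nothing specific to that child about the other.

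Two kinds of result are at stake, and their errors run in opposite directions. Change between visits is estimated more precisely than the model reports. Effects of child characteristics are estimated less precisely than it reports.

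**Working it through.** **The plan's own figure.** Inputs from Sample size and power considerations: difference 19.05, SD 38.1, two-sided alpha 0.05, power 0.90, ICC 0.1, 504 children in 24 preschools (504/24 = 21 each).
- Per arm without clustering: 2 × (1.960 + 1.282)² × (38.1/19.05)² = 84.06.
- Design effect: 1 + (21 − 1) × 0.1 = 3.0.
- Total: 2 × 84.06 × 3 = 504.4, against 504 stated. With 10% loss: 504/0.9 = 560, as stated.

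This rests on one measurement per child and the preschool ICC, so a child level does not alter it.

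**Set-up for the model check.** Total variance is 1 and preschool variance 0.1 (the plan's ICC). The correlation r between two values of one child is assumed to be 0.3 to 0.8. Preschool-by-visit variance is assumed to be zero. Each child has two outcome values. Within a preschool the variance is 0.9, and the same-child correlation is w = (r − 0.1)/0.9. If baseline has the same correlation with each follow-up, adjusting for it reduces w to c = w/(1 + w).

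**(a) Change from 6 to 12 months.** The correct variance of a change is proportional to 1 − k, with k = w (unadjusted) or k = c (adjusted). The two-level model uses 1. The ratio of model SE to correct SE is 1/√(1 − k), whether the change is compared between arms or assessed within one arm.

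**(b) Child-level terms over the two visits.** The correct variance is proportional to 1 + k and the model again uses 1. The ratio of model SE to correct SE is 1/√(1 + k). The type I error is 2 × [1 − Φ(1.96 × ratio)].

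| r | w | c | (a) unadjusted | (a) adjusted | (b) ratio and type I error, unadjusted | (b) ratio and type I error, adjusted |
|---|---|---|---|---|---|---|
| 0.3 | 0.222 | 0.182 | 1.13 | 1.11 | 0.90, 7.6% | 0.92, 7.1% |
| 0.5 | 0.444 | 0.308 | 1.34 | 1.20 | 0.83, 10.3% | 0.87, 8.7% |
| 0.7 | 0.667 | 0.400 | 1.73 | 1.29 | 0.77, 12.9% | 0.85, 9.8% |
| 0.8 | 0.778 | 0.438 | 2.12 | 1.33 | 0.75, 14.2% | 0.83, 10.2% |

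Both columns are shown because the covariate list names baseline BMI and accelerometer counts. It names no own baseline value for the other secondary outcomes.

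**(c) Arm effect averaged over the follow-ups.** The correct variance of a preschool mean with m children and T visits is σ²(preschool) + σ²(child)/m + σ²(error)/(Tm). In a balanced design the two-level model estimates this whole sum from the observed spread between preschools, because its preschool variance absorbs the child part. The SE is therefore about right.

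**What (a) means for research question 5.** Take 371 and 370 children (Recruitment and randomization), all measured at both follow-ups, and a true between-arm loss of 0.2 SD from 6 to 12 months. At r = 0.5 the correct SE is √[2 × 0.5 × (1/371 + 1/370)] = 0.0735, and 0.2/0.0735 = 2.72. The chance of missing the loss is 1 − Φ(2.72 − 1.96) = 22% with the correct SE. It is 1 − Φ(2.72 − 1.96 × 1.20) = 36% with the adjusted two-level SE and 1 − Φ(2.72 − 1.96 × 1.34) = 46% with the unadjusted one. At r = 0.7 the three figures are 6%, 16% and 45%. The 0.2 SD is illustrative and is not in the document.

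**Simulation.** The two-level model was fitted to 20 + 17 preschools of 20 children with two measurements, without baseline adjustment, 200 runs per setting. Empirical and model SE of the arm effect were 0.117/0.117, 0.119/0.122 and 0.128/0.123 at r = 0.3, 0.5 and 0.7. The type I error for arm by time was 3.0%, 1.5% and 0%. Many fits gave convergence warnings, so the conclusion rests on the formulas.

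**The case against.** The best defence is that this is loose counting in a condensed article. The abstract calls the models longitudinal, the covariates are placed at the individual level, and the child is called the unit of analysis. Nothing excludes a within-child residual covariance at level 1, and an unseen analysis plan may specify one. That stands as a possible intention. It does not settle the matter, because the article goes beyond leaving the structure open: it numbers the levels, and the child is not one of them.

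A reader might infer that repeated measurements are treated as fully independent. The document does not say so, and the preschool effect itself induces some correlation.

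A reader might also infer that no p-value or confidence interval from this model can be trusted. That fails for the main arm comparison, as (c) shows. A single 6-month outcome adjusted for baseline has one value per child and needs no child level.

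A type I error of 12 to 21% for child-level terms follows only if baseline is counted as a third outcome: with T = 3 the SE ratio is √(1 + 2r), or 1.26 to 1.55 for r = 0.3 to 0.7. The plan makes baseline a covariate.

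A type I error above 5% for arm by visit requires preschool-by-visit variance. In the simulation, assumed values of 0.05 and 0.10 at r = 0.5 gave 6.5% and 13%. The document gives no such variance, and a child intercept would not cure it. Such variance would also shrink the overstatement in (a) for the between-arm change.

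Finally, an SE that is too large is conservative for claims of increased activity. That is correct, but it does not help where non-significance is itself the claim, as in research question 5. Age, sex and SES are adjustment terms without hypotheses of their own, so the anti-conservative error matters mainly for the subgroup comparisons.

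**Conclusion.** Wrong as written, of moderate severity. The stated two-level structure omits the child and conflicts with the abstract's within-subject analysis. The 6-to-12-month change gets an SE that is too large by a factor of about 1.1 to 1.3 with baseline adjustment (1.1 to 2.1 without), which tilts research question 5 towards declaring effects sustained. Child-level terms, including the immigrant and overweight comparisons, get SEs that are too small, with a type I error of about 7 to 10% (8 to 14% without adjustment) instead of 5%.

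These sizes depend on the plan's ICC of 0.1, an assumed same-child correlation of 0.3 to 0.8, equal correlation between all visits and no preschool-by-visit variance. The direction of both errors holds throughout that range. The averaged arm effect, a baseline-adjusted 6-month comparison, the sample size and the power for the planned 0.5 SD difference are unaffected.

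**What to change.** Restate the model in Assessment of intervention effectiveness as visits (level 1) within children (level 2) within preschools (level 3), with random intercepts for child and preschool. An equivalent is a within-child residual covariance together with a preschool random effect. If the analysis plan already has this, correct the article's description to match.

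The cost is one sentence and one extra term in the model code. No new data and no change in sample size are needed.

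A preschool-by-visit random term and small-sample degrees of freedom for the 37 preschools are optional, separate refinements and not part of this correction.
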